#### Blinding

The researcher assistants, outcome assessors, statisticians, and subjects will be blinded to the group assignment. All participants will undergo press-needle therapy while lying on a bed in a tranquil clinic setting. For the control group, a nonpenetrating sham apparatus, similar in appearance to acupuncture needles, will be used to achieve blinding. Moreover, every participant will be asked about their experience subsequent to the acupuncture session to evaluate the efficacy of blinding. Unblinding of researchers is permitted only in exceptional circumstances, such as when there is a strong need to know about the actual treatment in order to manage the subject appropriately.

### Interventions

#### Experimental Group

Acupoints will be selected based on acupuncture combined with clinical experience [15]: main acupuncture points (BL2 Cuanzhu, TE23 Sizhukong, EX-HN5 Taiyang, and ST2 Sibai) and matching points (PC6 Neiguan, SP10 Xuehai, BL17 Geshu, BL18 Ganshu, BL23 Shenshu, SP6 Sanyinjiao, and K13 Taixi) (Figure 1). These points can exert a concerted effect to nourish the liver and kidneys, promote blood circulation, and dredge collaterals. Press-needle treatment will be performed by acupuncturists with more than 3 years of clinical experience. The acupuncturist will disinfect the skin around the acupoints (on the same side of the affected eye) with povidone iodine when the subject lies down on the treatment bed in a supine position. Disposable sterile press needles (0.2 mm in diameter and 0.6 mm in length; Seirin Corporation) will then be inserted into the right acupoints (Figure 1). The needles will be pressed so that they can adhere and be tied, the peelable paper will be removed, and the adhesive tape will be pressed down to ensure a secure fit. The needles will be left in place for 2 days, and participants will be asked to press the needles themselves 3-4 times/day, every 4 hours, for 1 minute each time to achieve deqi sensations, including soreness, numbness, heaviness, fullness, and aching.

#### Control Group

Sham press needles are the same as press needles but lack the needle element [9]. The procedures and manipulations carried out in the control group will be indistinguishable from those implemented in the experimental group. Subjects will be treated individually in a secluded room to prevent any disruptions from family members or other individuals.

#### Criteria for Discontinuing or Modifying Allocated Interventions

Participants will have the freedom to withdraw from the clinical study and opt for alternative treatments (eg, citicoline sodium tablets) if they believe their condition will not improve. Reasons for discontinuing treatment may include, but are not limited to, the following: (1) the pregnancy, (2) severe side effects or complications, (3) taking other medications during the study, (4) failure to comply with the study protocol, and (5) request for withdrawal for other reasons.

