**Methods:**

In total, 192 participants aged 18-75 years with GPCI from the Mianyang Central Hospital, the Mianyang Hospital of Traditional Chinese Medicine, and the Mianyang Wanjiang Eye Hospital will participate in this study. Participants will be allocated to 2 treatment groups (experimental and control groups) in a ratio of 1:1 and will undergo press-needle therapy and sham press-needle therapy, respectively, for the same 4-week period. Primary outcomes will include the best-corrected visual acuity (BCVA), optical coherence tomography angiography (OCTA), color Doppler flow imaging (CDFI), and visual field assessment results. Secondary outcomes will include the intraocular pressure (IOP) and traditional Chinese medicine (TCM) clinical symptom scales. The primary outcomes and safety assessments will be measured at baseline and 4 weeks thereafter, while the secondary outcomes will be measured at baseline and 1, 2, 3, and 4 weeks thereafter.

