### Recruitment Procedure

Potential participants with GPCI were recruited from the Mianyang Central Hospital (Sichuan, China), the Mianyang Hospital of Traditional Chinese Medicine (Sichuan, China), and the Mianyang Wanjiang Eye Hospital (Sichuan, China). We used the internet, hospital announcements, and posters to provide a hotline calling for potential volunteers. If patients were interested in our study, researchers informed them in detail of the purpose and content of the research and the benefits and risks of participating.

After screening, participants meeting the inclusion criteria will be enrolled. Frequent follow-up phone calls are an important aspect of adherence monitoring. Every participant will have the right to withdraw from the trial at any time. Furthermore, it will be obligatory for all subjects to sign an informed consent document prior to commencement of the trial.

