### Outcome Measures

#### Primary Outcome Measures

The primary outcomes will enable us to evaluate improvements in visual function, retinal blood circulation, and retrobulbar blood vessel circulation due to press-needle therapy. The outcomes will be as follows:

The mean change in the BCVA will be measured at baseline and 4 weeks thereafter.The mean change in the values of the pattern standard deviation (PSD), mean defect, and square root of loss variance (sLV) will be determined using an Octopus 900 perimeter at baseline and 4 weeks thereafter.The whole-image vessel density (wiVD), radial peripapillary capillary vessel density (RPCVD), superficial macula vascular density (smVD), parafoveal vessel density (paraVD), perifoveal vessel density (periVD), macular ganglion cell complex (mGCC), and peripapillary retinal nerve fiber layer (pRNFL) will be determined using optical coherence tomography angiography (OCTA) at baseline and 4 weeks thereafter.The ophthalmic artery (OA), central retinal artery (CRA), short posterior ciliary artery (SPCA), peak systolic velocity (PSV), end diastolic velocity (EDV), and resistance index (RI) will be determined using CDFI at baseline and 4 weeks thereafter.

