#### Quality Control

To guarantee the quality of the proposed experiment, a unified and standardized training program will be conducted for the researchers in each role prior to commencement of the study. Subsequently, the researchers will be subjected to a proficiency assessment, and only those deemed competent will be permitted to participate in the study. Furthermore, to enhance participant compliance, regular health education activities will be conducted, humane care will be enhanced, and a long-term follow-up plan will be developed. Finally, in accordance with the requirements set forth in the Specifications for Quality Control and Quality Assurance of Clinical Research in Chinese Medicine [19], a 4-level quality monitoring system will be established to monitor the clinically collected data on a regular monthly basis, thereby ensuring the authenticity and reliability of the study results.

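### Switching treatment for expected non-improvement is worded as leaving the study, which forfeits the only post-baseline primary measurement (week 4)

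*Protocol article*

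**What the plan says.** The section Criteria for Discontinuing or Modifying Allocated Interventions has two sentences. The first gives participants the freedom to "withdraw from the clinical study and opt for alternative treatments (eg, citicoline sodium tablets) if they believe their condition will not improve". The second begins "Reasons for discontinuing treatment may include, but are not limited to, the following" and lists five reasons: pregnancy, severe side effects or complications, "taking other medications during the study", non-compliance with the protocol, and "request for withdrawal for other reasons".

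On timing, the abstract's Methods paragraph states: "The primary outcomes and safety assessments will be measured at baseline and 4 weeks thereafter". The Primary Outcome Measures section repeats this for each group of outcomes, for example "The mean change in the BCVA will be measured at baseline and 4 weeks thereafter". Perimetry, OCTA and CDFI have the same two time points. Only intraocular pressure and the TCM symptom score are also measured at weeks 1, 2 and 3.

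The nearest provisions on retention are in Recruitment Procedure ("Frequent follow-up phone calls are an important aspect of adherence monitoring") and Quality Control ("a long-term follow-up plan will be developed"). The Discussion adds that methylcobalamin is given in both arms, partly to limit loss of patients.

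**The concern.** Stopping the allocated treatment and ending participation are different events. A participant can give up the needles, start citicoline and still be willing to have visual acuity, visual field and blood flow measured at week 4. The discontinuation section does not offer that combination to someone who expects no improvement. It pairs the other treatment with leaving the study.

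The loss matters more here than in a trial with repeated primary measurements. Someone who exits before week 4 leaves no intermediate primary value to draw on. The stated trigger, a belief that the condition will not improve, is plausibly related to outcome, so such values may not be missing at random. No later analysis can recover a measurement that was never taken. With one post-baseline time point, the carry-forward rule in Statistical Analysis can only supply the baseline value, which is a change of zero. Whether that rule is sound is a separate matter and is not counted here.

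**Working it through.** **Reading the text**

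1. The first sentence of the discontinuation section ties another treatment, sought because of expected non-improvement, to withdrawal from the study.
2. The abstract and Primary Outcome Measures give every primary outcome one post-baseline time point, week 4.
3. So a participant who takes the route in step 1 before week 4 has no post-baseline primary value.
4. The adherence calls, the follow-up plan and methylcobalamin in both arms may reduce how many leave. None of them provides a week-4 visit for someone who has left.

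**How many could be affected**

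The article gives no number for this route. Two all-cause figures limit it loosely.

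- Dropout allowance (Sample Size Calculation): 160 × 0.20 = 32 and 160 + 32 = 192, as stated. As a share of those recruited, 32/192 = 16.7%, or 16 of 96 per arm.
- Counts in the abstract and Results: 220 recruited and 192 (87.3%) to complete. 220 − 192 = 28 and 28/220 = 12.7%, or 14 of 110 per arm if split evenly. The wording is ambiguous: the abstract also says that the remaining participants will serve exploratory analyses, so the 28 may not be losses.

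**Illustration of scale**

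Assumptions, none from the document: leavers would have scored d = 0.5 SD below completers of their own arm; this holds in one arm only; the other arm loses the same number, but its leavers resemble its completers. With a fraction p leaving, the completer mean exceeds the whole-arm mean by p × d. The standard error of the difference, in SD units, is √(2/n) with n completers per arm.

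| Case | Shift | SE | Shift/SE |
|---|---|---|---|
| 16 of 96 | (16/96) × 0.5 = 0.083 SD | √(2/80) = 0.158 | 0.53 |
| 14 of 110 | (14/110) × 0.5 = 0.064 SD | √(2/96) = 0.144 | 0.44 |
| 4 of the 16 losses per arm arise from this route | (4/96) × 0.5 = 0.021 SD | √(2/80) = 0.158 | 0.13 |
| Same p and d in both arms | 0 | – | 0 |

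The sign depends on which arm has the poorer leavers. The first two rows attribute every loss to this one route and are therefore upper cases under the assumed d. All rows describe a completers comparison. They do not describe an FAS in which leavers are kept with baseline carried forward.

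**The case against.** The strongest defence is that the first sentence is permissive. Participants may always withdraw, the article says so in Recruitment Procedure, and this sentence applies that right to people who want something else. It does not say that a switcher must leave or may not be measured. That stands as far as the right goes, and the right is proper. But the section should say what happens when treatment changes, and for expected non-improvement the only path it describes is out of the study.

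Three stronger readings are tempting, and the document does not support them.

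- *Follow-up ends for everyone who stops the needles.* The article does not say so. The list gives reasons for stopping treatment, and the outcome sections schedule week 4 without excluding those who have stopped. For the first four reasons the question is left open. A condensed article may leave it to the full protocol, so that silence is no error.
- *The same switch is classed once as study exit and once as stopping treatment.* This would require the third listed reason to be the same event as in the first sentence. It can equally describe someone who is still in the study and takes another drug. Only the fifth reason clearly mixes the two terms.
- *28 participants have been lost.* The wording does not establish this.

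The matched sham (Blinding; Control Group) also counts against a large effect: it makes leaving that differs by arm less likely, though it does not exclude it. The article expects few missing data and reports good retention.

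**Conclusion.** The point holds in a limited form. As worded, the route for a participant who expects no improvement is to leave the study. If taken before week 4, it removes that participant's only post-baseline primary value, for a reason plausibly linked to outcome. That follows directly from the discontinuation section and the measurement schedule.

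How often this happens, and the size and direction of any bias, cannot be determined from the document. Any bias is probably small given the matched sham. The illustrative shifts of 0.021 to 0.083 SD rest on an unsourced 0.5 SD deficit confined to one arm; they show scale only. A reader might infer from them that the trial's result will be biased, and they do not show that. The point is a cheap improvement in the rule for conduct; no sample-size figure depends on it.

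**What to change.** Reword the discontinuation section so that stopping or switching treatment is separate from withdrawing consent.

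- Ask everyone who stops or switches but still consents to attend the week-4 visual acuity, perimetry, OCTA, CDFI and safety assessments already scheduled.
- Record the date, the reason and any alternative treatment.
- Analyse observed week-4 values by allocated arm in the FAS, including any already obtained after stopping. Keep the per protocol set for the on-treatment effect.

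The cost is an amendment, plus extending the planned adherence calls to cover attendance at week 4. Those who withdraw consent remain missing.

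There are two drawbacks. Post-switch values dilute the needle effect in the FAS, which then estimates the effect of being allocated to needles whether or not the participant switches. New visits help only participants not yet past week 4. These may be few: the Results section reports 220 recruited by October 2024, and it gives both March 2024 and September 2025 as the end of recruitment. Including values already obtained after stopping needs no new visit at any stage.

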### Outcome Measures

#### Primary Outcome Measures

The primary outcomes will enable us to evaluate improvements in visual function, retinal blood circulation, and retrobulbar blood vessel circulation due to press-needle therapy. The outcomes will be as follows:

The mean change in the BCVA will be measured at baseline and 4 weeks thereafter.The mean change in the values of the pattern standard deviation (PSD), mean defect, and square root of loss variance (sLV) will be determined using an Octopus 900 perimeter at baseline and 4 weeks thereafter.The whole-image vessel density (wiVD), radial peripapillary capillary vessel density (RPCVD), superficial macula vascular density (smVD), parafoveal vessel density (paraVD), perifoveal vessel density (periVD), macular ganglion cell complex (mGCC), and peripapillary retinal nerve fiber layer (pRNFL) will be determined using optical coherence tomography angiography (OCTA) at baseline and 4 weeks thereafter.The ophthalmic artery (OA), central retinal artery (CRA), short posterior ciliary artery (SPCA), peak systolic velocity (PSV), end diastolic velocity (EDV), and resistance index (RI) will be determined using CDFI at baseline and 4 weeks thereafter.

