### Statistical Analysis

Statistical analysis will be conducted independently by statisticians. The data will be presented as means (SDs). IBM SPSS 22.0 statistical software will be used. All statistical tests will be 2-sided tests, and the limit for statistical significance will be set at *P*<.05. The chi-square test will be performed for categorical variables, the independent Student *t* test will be used for measurement data, and the rank-sum test will be used for grade data. To evaluate the covariate balance, baseline characteristics will be summarized and compared between the experimental group and the control group using simple descriptive statistics.

Due to the expected low number of missing data, we will deal with missing data by transferring the last data item to the final dataset. This participant's data will be invalidated in the full analysis set (FAS), and this case will not be included in the per protocol set (PPS). Finally, the statistical significance of the FAS and PPS will be analyzed. A consistent statistical significance will indicate a significant difference.

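### Between 17 and 20 variables are all primary, each tested at two-sided P<.05 with no lead variable or success rule, so the chance of a false positive primary result is several times 5%

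*Protocol article*

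**What the plan says.** The Abstract (Methods) names four domains jointly: "Primary outcomes will include the best-corrected visual acuity (BCVA), optical coherence tomography angiography (OCTA), color Doppler flow imaging (CDFI), and visual field assessment results". The section Primary Outcome Measures opens with "The primary outcomes will enable us to evaluate improvements in visual function, retinal blood circulation, and retrobulbar blood vessel circulation due to press-needle therapy" and then lists:

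- **Acuity, 1 variable:** "The mean change in the BCVA will be measured at baseline and 4 weeks thereafter".
- **Perimetry, 3 variables:** "pattern standard deviation (PSD), mean defect, and square root of loss variance (sLV").
- **OCTA, 7 variables:** five vessel densities, the macular ganglion cell complex and the peripapillary nerve fiber layer.
- **CDFI:** the ophthalmic artery, then "central retinal artery (CRA), short posterior ciliary artery (SPCA), peak systolic velocity (PSV), end diastolic velocity (EDV), and resistance index (RI").

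Neither place marks one variable as the main one. Neither gives an order of testing, a composite, or a rule on how many variables or domains must succeed.

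The section Statistical Analysis makes all tests two-sided, and "the limit for statistical significance will be set at *P*<.05". Measurement data are compared by independent t test. The section ends with one further condition: significance is to be examined in both the FAS and the PPS, and consistent significance is what counts as a difference.

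The Sample Size Calculation uses one binary effective rate at α=.05. That rate is not among the listed outcomes.

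**The concern.** A trial with many primary variables and no success rule lets a positive primary result be declared on whichever variable crosses .05. The Conclusion gives the purpose as verifying that the therapy improves visual function and ocular circulation, which is a confirmatory claim. The 5% level then applies to each variable singly and not to that claim. The sample size calculation does not settle which variable is meant, because its endpoint is not on the list.

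This is not a detail left to a fuller protocol or an analysis plan. Which outcomes are primary, and what counts as significant, are both fixed in this article.

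**Working it through.** The document states no family-wise error, so there is no figure of its own to reproduce.

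**Count.** Acuity 1 + perimetry 3 + OCTA 7 + CDFI 9 (3 arteries × 3 parameters) = 20. If the six CDFI terms are counted as they stand, 1 + 3 + 7 + 6 = 17.

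**Independent tests, one analysis set.** The chance of at least one P<.05 among k true nulls is 1 − 0.95^k.

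- k = 20: 1 − 0.95^20 = 64.2%, with 20 × 0.05 = 1.0 false positive expected.
- k = 17: 1 − 0.95^17 = 58.2%.
- k = 4 (one variable per domain): 1 − 0.95^4 = 18.5%.

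**Correlated tests, one analysis set, k = 20.** The documents give no correlations. Simulated normal test statistics with an assumed uniform correlation give:

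| Uniform correlation (assumed) | Chance of at least one P<.05 |
|---|---|
| 0.3 | 54% |
| 0.5 | 42% |
| 0.7 | 29% |
| 0.9 | 16% |

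**Adding the FAS-and-PPS condition.** Assume the PPS is 80% of the FAS. The two test statistics for one variable then correlate at √0.8 = 0.894. Under no effect, the chance that both are significant in the same direction is 0.0291 per variable, of which half (0.0146) favors the therapy.

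- Independent variables, either direction: 1 − (1 − 0.0291)^20 = about 45%.
- Independent variables, favoring the therapy only: 1 − (1 − 0.0146)^20 = about 25%.

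Simulation with assumed correlations within and between the four domains (k = 20) gives:

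| Within / between domains (assumed) | FAS alone, either direction | FAS and PPS, either direction | FAS and PPS, favoring therapy |
|---|---|---|---|
| 0.5 / 0.2 | 51% | 35% | 18% |
| 0.7 / 0.2 | 43% | 29% | 15% |
| 0.9 / 0.2 | 31% | 20% | 10% |

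The nominal levels for comparison are 5% in either direction and 2.5% in favor of the therapy. The condition lowers the error but does not bring it near either level.

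**The case against.** The strongest reply is that the written rule is stricter than P<.05 alone, because FAS and PPS must agree. That stands. The 64% figure belongs to a looser rule, and the working therefore shows both.

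Four stronger readings are tempting, and the documents do not support them.

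- **A reader might infer that a false positive is more likely than not.** That holds only for independent or weakly to moderately correlated variables on one analysis set. With the FAS-and-PPS condition, every case computed is below one half.
- **A reader might take 20 as the stated count.** It is a sensible reading of the CDFI list, but the literal count is 17.
- **A reader might infer that the protocol declares success on any one variable.** It does not say so; it gives no success rule. If success needed at least one of the 4 acuity and perimetry variables and at least one of the other 16, independence on one analysis set would give 0.185 × 0.560 = about 10%. That rule is not written either.
- **A reader might infer that no positive result could be trusted.** The variables are listed in advance, so a result below 0.05 / 20 = 0.0025 would survive Bonferroni over the whole list.

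The two-sided figures also count results against the therapy. The one-directional column answers that point. It gives 10% to 18% under the tabulated correlations and 25% if independent, against 2.5%.

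**Conclusion.** The point holds. The article makes 17 to 20 variables primary, fixes two-sided P<.05 for each, and gives neither a success rule nor a correction across outcomes.

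If any one variable can be claimed, the chance of a false positive primary result is at most 64% (58% for 17 variables) on one analysis set. Under the FAS-and-PPS condition it is about 45% if independent and about 35% to 20% under the correlations considered. These sizes rest on three assumptions: the correlations, a PPS of 80% of the FAS, and the any-one reading of success. Across the scenarios with the FAS-and-PPS condition, the error is at least about four times nominal in either direction (20% against 5%) and in favor of the therapy (10% against 2.5%).

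This should be fixed before unblinding. As written, one significant variable from the list could be reported as a positive primary outcome.

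**What to change.** Before database lock and unblinding, the sponsor should adopt one of two structures.

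1. **One primary variable at two-sided .05**, with one blood-flow variable as key secondary, tested only if the primary succeeds. The choice of primary is the sponsor's; Octopus mean defect is only an example.
2. **One named variable per domain**, four in all, with Holm at an overall .05.

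Either way, the remaining variables become secondary or exploratory, reported with estimates and confidence intervals and without claims of significance.

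The section Ethical Considerations requires a new protocol version to go to the ethics committee when outcomes or analyses change. The registration should be updated to match. The Results section reports 220 recruited by October 2024, so the change should be reported as made after recruitment but before unblinding. The Discussion says that principal investigators, statisticians and assessors stay blinded until database lock, which makes a credible late choice possible.

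**Costs.** Fewer results can be called significant primary findings. Holm starts at .05 / 4 = .0125, where an endpoint with 90% power at .05 has about 77%. The chosen primary has no stated power in either structure, because the trial was sized on a binary effective rate that is not on the list. The power available for the chosen variable should therefore be worked out and stated with the change. No new data or participants are needed to apply the testing rule itself.
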